## Abstract

**Background:**

This randomised controlled trial (RCT) with two parallel arms will evaluate the efficacy of an internet-delivered six-lesson 10-week cognitive behavioural therapy (iCBT) intervention for posttraumatic stress disorder (PTSD). It will also investigate the association between changes in PTSD symptoms, intolerance of uncertainty (IU) and emotion regulation.

**Methods/Design:**

Patients with PTSD will be recruited via the research arm of a not-for-profit clinical and research unit in Australia and randomised to a treatment group or waitlist control group. The minimum sample size for each group (alpha 0.05, power 0.80 for a *g* of 0.47) was identified as 72, but 10 % more will be recruited to hedge against expected attrition. PTSD diagnosis will be determined using the PTSD module from the Mini International Neuropsychiatric Interview version 5.0.0. The PTSD Checklist – Civilian version (PCL-C) will be used to measure PTSD symptoms (the primary outcome measure), with the Intolerance of Uncertainty Scale 12-item version (IUS-12) and the Emotion Regulation Questionnaire (ERQ) used to measure intolerance of uncertainty and emotion regulation, respectively. The PCL-C will be administered to the treatment group before each lesson of the PTSD program and at 3-month follow-up. The IUS-12 and ERQ will be administered before lessons 1 and 4, at post-treatment and at 3-month follow-up. The waitlist control group will complete these measures at week 1, week 5 and week 11 of the waitlist period. PTSD program efficacy will be determined using intent-to-treat mixed models. Maintenance of gains will be assessed at 3-month follow-up. Mediation analyses using PROCESS will be used to examine the association between change in PTSD symptoms over treatment and change in each of IU and emotion regulation ability in separate analyses.

**Discussion:**

The current RCT seeks to replicate previous efficacy findings of iCBT for PTSD in a formally assessed PTSD sample from the general population. Findings may point to future lines of enquiry for the role of IU and emotion regulation in the mechanism of PTSD symptom change during CBT.

**Trial registration:**

Australian New Zealand Clinical Trials Registry: ACTRN12614001213639, registered 18 November 2014. This trial protocol is written in compliance with the Standard Protocol Items: Recommendations for Interventional Trials (SPIRIT) guidelines.

## Background

Posttraumatic stress disorder (PTSD) can follow experiencing a traumatic event in which the individual experiences or witnesses severe threat to life or physical safety. It is characterised by recurrent intrusive thoughts or memories of the traumatic event, avoidance of trauma reminders, elevated physiological arousal and negative changes in thoughts and mood [1]. The lifetime prevalence of PTSD is approximately 7 % in the general population [2–4]. It has a chronic course when untreated – up to one third of those with PTSD remain symptomatic for 30 years [5]. The impact of the disorder on the individual is significant. Compared to those without the disorder, PTSD is independently associated with: greater prevalence of physical health conditions, such as respiratory disease, cardiovascular disease, cancer and gastrointestinal illnesses [6], but see [7]; increased comorbidity of mental health conditions, such as anxiety disorders and depression [8]; and increased risk of suicidal behaviour [9]. Taken together, these data indicate a significant individual impact from the disorder, as well as societal cost in terms of burden of disease.

Cognitive behavioural therapy (CBT) is the psychological treatment of choice for PTSD and is recommended by best-practice treatment guidelines e.g. [10, 11]. CBT typically involves confrontation with, and processing of, the trauma memory in a safe, gradual manner; identification and restructuring of problematic beliefs; and dearousal skills. There is strong research evidence for use of these CBT techniques to treat PTSD in terms of magnitude of symptom reduction from pre-treatment levels, and diagnostic recovery [12–15]. Despite this evidence, those with PTSD are an underserviced population. The majority of those with PTSD do not seek treatment and those seeking treatment do so with significant delay [16]. Associated treatment barriers include stigma, cost, geography and insufficient treatment availability [17]. Indeed, McLean and Foa [17] have noted that development of effective and efficient delivery systems for evidence-based PTSD treatments remains a key challenge in the trauma field.

Attempting to counter these difficulties, recent efforts have examined internet-based delivery of empirically supported treatment for PTSD symptomatology. Clinical research has shown that internet-based delivery of cognitive behavioural therapy (iCBT) has utility for treating PTSD symptoms to an extent approximately equivalent to face-to-face treatment [18–21]. These treatments are typically divided into five to ten lesson modules, delivered over several weeks, with some form of therapist support (e.g. email or phone).

Though iCBT appears promising in treating PTSD, variation in experimental design and course structure means further clinical trials are warranted. Moreover, the role of emotion process variables in PTSD response to iCBT has not been examined. To date, published studies have either not included a control group e.g. [21], not formally diagnosed PTSD e.g. [19], been based on a self-help mode of treatment e.g. [22] or required significant initial therapist input to provide psychoeducation and explain treatment components to the patient e.g. [18]. Only two published randomised controlled trials (RCT) to date have examined the efficacy of iCBT for PTSD in a formally diagnosed PTSD sample from the general population [20, 23]. However, those studies did not examine mediators of symptom change. Therefore, in order to extend and validate iCBT for PTSD, the proposed study will conduct an RCT to examine the clinical efficacy of this approach and mediators of PTSD symptom change.

Emerging evidence suggests intolerance of uncertainty (IU) as a transdiagnostic construct central to the expression of psychopathology [24–26]. IU is the tendency to respond to uncertainty with a negative emotional and cognitive set and corresponding avoidance and risk mitigation behaviour [27]. Recent research has indicated reduction in IU is associated with anxiety and depressive symptom reduction following psychological treatment [28]. With respect to PTSD, IU has been positively associated with severity of arousal, avoidance and numbing symptoms [29]. However, the association between PTSD treatment and variation in IU has not been investigated, nor has the relationship between change in IU and PTSD symptoms over treatment. Therefore, the current study will examine these relationships in PTSD.

Finally, recent work has investigated the role of emotion regulation in PTSD treatment outcome. Emotion regulation is the ability to actively influence the timing, experience and expression of emotion. Emotion regulation skills training has been shown to reduce dropout and enhance outcome from subsequent exposure-based PTSD treatment [30, 31]. Moreover, exposure-based treatment for PTSD has been associated with enhancement in emotion regulation [32]. However, it remains unclear whether emotion regulation before treatment predicts an individual’s response to treatment. While Wisco et al. [33] found better pre-treatment emotion regulation skills were not predictive of enhanced PTSD treatment outcome, that treatment omitted in vivo exposure and cognitive restructuring, treatment components to which emotion regulation may be conceptually related. The association between emotion regulation and treatment outcome in an internet-delivered intervention for PTSD comprising written exposure, in vivo exposure and cognitive restructuring has not been investigated. As such, this study seeks to examine the role of emotion regulation in PTSD symptom response to this treatment approach.

### Objectives

The current Standard Protocol Items: Recommendations for Interventional Trials (SPIRIT)-compliant [34] protocol outlines the methodology of a CONSORT-compliant [35] RCT, the primary objective of which is to establish the efficacy of the iCBT program for PTSD. Secondary objectives are to examine change in IU and emotion regulation ability following the iCBT program and the association between change in each of these constructs and PTSD symptom change following the PTSD program.

The proposed iCBT program aims to reduce psychological distress and PTSD symptoms in those with PTSD. It comprises psychoeducation about the trauma reaction and how it is maintained after the event by particular patterns of thinking, feeling and behaving. Dearousal skills are taught and practiced. Participants are taught ways to identify and change unhelpful thoughts about the trauma. They will be habituated to their challenging trauma memories using a series of brief structured writing assignments and taught graded exposure methods to re-enter feared situations. Finally, relapse prevention will cover continued skills practice and instruction on independent management of potential future setbacks. These elements have been incorporated into standard CBT-based treatment for PTSD both in internet and face-to-face formats [12, 18–21, 36–38], but have been adapted for the proposed internet treatment program.

Hypotheses are as follows: (1) patients receiving iCBT for PTSD will show greater mean symptom reduction on a standardised PTSD measure than a waitlist control group during treatment and at the end of treatment (the primary endpoint), with preserved symptom reduction at 3-month follow-up; (2) IU will be less at post-treatment than pre-treatment; (3) reduction in IU over treatment will be associated with reduction in PTSD severity; (4) emotion regulation will be greater at post-treatment than pre-treatment; and (5) increased emotion regulation after treatment will be associated with reduced PTSD severity after treatment.

## Methods/Design

### Study setting

The Clinical Research Unit for Anxiety and Depression (CRUfAD) is a non-profit joint initiative of St. Vincent’s Hospital and the University of New South Wales, School of Psychiatry in Sydney, Australia. CRUfAD specialises in the development, evaluation, and dissemination of evidence-based CBT programs via the internet. This RCT will be conducted within the Virtual Clinic, CRUfAD’s clinical research arm (www.virtualclinic.org.au). The mode of internet recruitment and delivery enables potential participants from all Australian states to apply for enrolment in the current trial.

### Participants and recruitment

Participants will be recruited through flyers, paid print and internet advertising. Applicants will first complete online screening questionnaires about symptoms and demographic details (see Fig. 1 for a participant flow chart). Inclusion criteria are as follows: meet diagnostic criteria for PTSD; computer, internet and printer access; Australian resident; fluent in written and spoken English; willing to provide name, phone number and address, and to provide the name and address of a local general practitioner. Exclusion criteria are as follows: trauma occurrence within the past 4 weeks; non-resident of Australia; less than 18 years of age; currently receiving treatment for trauma/PTSD; frequent suicidal ideation (indicated by a score of 3 to item 9 of the Patient Health Questionnaire 9-item version (PHQ9)); regularly using illicit drugs or regularly consuming more than three standard drinks per day; psychotic disorder or taking atypical antipsychotics or benzodiazepines; if taking medication for anxiety or depression, has been taking the same dose for less than 1 month or intending to change the dose during the course of the program; currently highly dissociative (indicated by score ≥40 on the Dissociative Experiences Scale as per Spence et al. [20]); current or pending medicolegal proceedings associated with the reported trauma; applying for, or receiving, Workers Compensation associated with their trauma or PTSD. Excluded applicants will receive information on alternative services and will be encouraged to discuss their symptoms with their physician. Applicants who pass the screening phase will be telephoned for a diagnostic interview using the PTSD module from the Mini International Neuropsychiatric Interview version 5.0.0 (MINI) [39] to determine whether they meet diagnostic criteria for PTSD. All interviews will be conducted by a registered Clinical Psychologist (AA) or Clinical Trials Manager (JS) under the guidance of the Clinical Psychologist and trained in administration of the diagnostic interview. Applicants who satisfy all inclusion criteria will be informed of the study design and will complete an electronic informed consent prior to enrolling in the trial. Information from the diagnostic interview will be used for research purposes only for those participants who provide informed consent. All participants will be informed in writing that they may withdraw from the study (i.e. choose to cease program enrolment or choose for their data to be excluded from the RCT) at any time without jeopardising their relationship with St. Vincent’s Hospital or the University of New South Wales. Further, those participants randomised to the waitlist control group will be informed that should they commence a trauma-focused intervention outside of the trial, their data will be omitted from the RCT.

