### Randomisation

Accepted participants will be randomised based on an allocation sequence generated by an independent person not involved in the study via a true randomisation process (www.random.org). Numbers corresponding to treatment group (1) or the waitlist control group (2) will be placed in sealed opaque envelopes bearing the sequential order number to ensure participant allocation based on the pre-determined randomisation sequence. A member of the research team will open the envelope after the diagnostic interview.

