### Participant monitoring

The Clinical Trials Manager of CRUfAD and a member of the research team will oversee participant monitoring. Symptom severity of the target disorder and general distress levels are measured before, during, and immediately upon completing the PTSD program based on empirically validated standardised internet-delivered symptom measures. Participants will be sent automated emails at the completion of each lesson to encourage skills practice. Patient queries throughout the program are primarily addressed by email contact from the clinician (AA) or the Clinical Trials Manager (JS). If clinically indicated, or if a patient’s K10 and/or PHQ9 or PCL-C scores deteriorate, the clinician makes telephone contact. If a participant misses a lesson, a member of the research team will send an email reminder (via the Virtual Clinic system) or will make telephone contact to remind the participant to complete the lesson.

The treatment group will be required to complete the iCBT program within 10 weeks to remain in the trial. Adherence is monitored throughout the program. Once enrolled, a participant can elect to discontinue at any time. A participant may be withdrawn from the trial (typically meaning course access will be closed) for the following reasons: lack of computer and internet access; change in prescribed medication for anxiety or depression; change in medication status of exclusion medications; suicidality or clinical risk; failure to complete baseline questionnaires; failure to commence the PTSD program. Lack of adherence throughout the iCBT program is not a specified reason for participant withdrawal, although a participant may withdraw voluntarily. Those in the waitlist control group will be required to complete questionnaires at weeks 1, 5 and 11 of the waitlist period to remain in the RCT. The waitlist control group will have access to the iCBT program immediately at the conclusion of the waitlist period. All reasons for withdrawal status will be documented.

To promote participant retention, participants are reminded that data collection is an important aspect of research and enables the research team to track their progress and to evaluate the program. Any adverse events will be reported to the Director of CRUfAD (GA) and to the Human Research Ethics Committee (HREC) of St Vincent’s Hospital, the responsible body for initiating a clinical trial audit.

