### Statistical methods

Power calculations were informed by calculation of effect size data from Spence et al. [20], providing a between-group effect corresponding to Hedges’ g of 0.47. The minimum sample size for each group (alpha set at 0.05, power at 0.80) was identified as 72, but at least 10 % more will be recruited to hedge against expected attrition. All analyses will be conducted at conclusion of the trial period (i.e. after all participants in the treatment group have completed the iCBT program). Significance testing of group differences regarding demographic data and pre-treatment measurements will be conducted using analysis of variance (ANOVA) and χ2 where the variables consist of nominal (or categorical) data. Intent-to-treat (ITT) mixed models using restricted maximum likelihood (REML) estimation will be used to account for missing data due to participant drop-out. Mixed models do not assume that the last measurement is stable (the last observation carried forward assumption) [63]. REML models are appropriate for RCTs with multiple time points and pre-to post-only designs [64]. The assumption that data are missing at random (MAR) will be evaluated using binary logistic regression to predict drop-out (0 = no drop-out, 1 = drop-out) and by comparing these two groups on baseline measures. Significant effects will be followed up with pairwise contrasts comparing mean pre-treatment to mean post-treatment scores. Complete-case analyses of the primary hypotheses using data from participants who complete all six lessons of the PTSD program will also be conducted. The effect of potential treatment moderators (e.g. time post-trauma, number of traumatic events) will be evaluated by including baseline variables of interest as a covariate and interaction term in separate mixed models analyses. Analyses will be performed in IBM SPSS version 21. Effect sizes will be calculated between groups (Hedges’ g) and within groups (Cohen’s d, adjusting for the repeated measures correlation) using the pooled standard deviation and adjusted for sample size.

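### Waitlist participants who start outside trauma therapy have their data omitted after randomisation, so the primary analysis is not intent-to-treat as labelled; two further rules on remaining in the trial are ambiguous

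*Protocol article*

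**What the plan says.** Statistical methods names the main analysis: "Intent-to-treat (ITT) mixed models using restricted maximum likelihood (REML) estimation will be used to account for missing data due to participant drop-out". The Abstract uses the same intent-to-treat label. Statistical methods also plans to model who drops out, to compare drop-outs with the others at baseline, and to add a completer analysis: "Complete-case analyses of the primary hypotheses using data from participants who complete all six lessons of the PTSD program will also be conducted".

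Participants and recruitment says that those randomised to the waitlist will be told that "should they commence a trauma-focused intervention outside of the trial, their data will be omitted from the RCT". No matching statement is made for the iCBT arm. The same section separately lets any participant choose to have their data excluded.

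Under Randomisation, "A member of the research team will open the envelope after the diagnostic interview", so therapy started during the waiting period follows allocation.

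Participant monitoring adds two conditions, one per arm. For iCBT: "The treatment group will be required to complete the iCBT program within 10 weeks to remain in the trial". For the waitlist, members are "required to complete questionnaires at weeks 1, 5 and 11 of the waitlist period to remain in the RCT". It also says "Lack of adherence throughout the iCBT program is not a specified reason for participant withdrawal", and it introduces withdrawal by the team with "A participant may be withdrawn from the trial (typically meaning course access will be closed) for the following reasons".

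**The concern.** Intent-to-treat means that randomised participants are compared in the arms to which they were allocated, whatever treatment they go on to receive. A rule that removes people from one arm because of a treatment choice made after allocation breaks that. The choice is unlikely to be random: participants know their allocation, have diagnosed PTSD and wait until week 11. Those who look for therapy elsewhere may be more distressed, or more motivated and already improving. The retained waitlist is then a selected group set against an iCBT arm with no such rule.

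A likelihood-based mixed model under missing at random uses what a participant has already contributed. The omission rule covers the participant's data without limit, so baseline and week-5 scores would go as well as week 11. The planned drop-out regression could not reveal the problem either, because the people concerned would not be in the file.

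The two conditions under Participant monitoring raise a related question: does someone who does not remain in the trial also leave the analysis? The text does not settle it.

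**Working it through.** **1. The plan's own figure.** Inputs from Statistical methods: g = 0.47 (SD = 1 on the standardised scale), alpha 0.05, power 0.80. For a two-sided comparison of two means:

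n = 2 × (1.960 + 0.842)² / 0.47² = 71.1, rounded up to 72 per group.

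The t-based solution is 72.04, with power 0.7998 at n = 72. The stated 72 is reproduced; a one-sided calculation would give 56. Adding 10% gives 72 × 1.10 = 79.2, or 72 / 0.90 = 80, so about 80 per arm.

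**2. Shift caused by the omission rule.** Let a share f of the waitlist be omitted, with a mean k SD away from those retained. The full-arm mean is (1 − f) × retained + f × (retained + k) = retained + f × k. The retained mean, and with it the between-group contrast, is therefore off by f × k SD. The documents give neither f nor k; both are assumed.

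| f | Shift, k = 0.5 | As % of 0.47 | Shift, k = 0.8 | As % of 0.47 |
|---|---|---|---|---|
| 5% | 0.025 | 5% | 0.04 | 9% |
| 10% | 0.05 | 11% | 0.08 | 17% |
| 20% | 0.10 | 21% | 0.16 | 34% |

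The sign depends on who leaves. If the omitted members have worse symptoms, the retained waitlist looks better and the effect shrinks; if they are improving, it grows. With a true g of 0.47, the extreme case (f = 20%, k = 0.8) gives 0.47 − 0.16 = 0.31 or 0.47 + 0.16 = 0.63.

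**3. Rejection rate with no true effect.** With 80 randomised per arm, SE = √(1/80 + 1/(80(1 − f))), and the test statistic is centred on f × k / SE instead of zero. For k = 0.5:

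- f = 5%: SE 0.160, centre 0.156, rejection 5.3%
- f = 10%: SE 0.162, centre 0.308, rejection 6.1%
- f = 20%: SE 0.168, centre 0.596, rejection 9.1% (9.2% by the normal approximation)

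For k = 0.8 the rates are about 5.7%, 7.8% and 16%.

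**4. Power.** Omission from the waitlist alone, at g = 0.47 and two-sided 0.05: 80 v 72 (10% omitted) gives 0.82; 80 v 64 (20% omitted) gives 0.795. The planned value is 0.80.

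**5. The other two rules, by comparing the text.**

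- *Ten weeks.* Finishing in time is a condition for remaining in the trial, yet poor adherence is said not to be a withdrawal reason. Both statements stand in Participant monitoring, and a participant who progresses slowly falls under each.
- *Questionnaires.* Completing all three is a condition for waitlist members to remain in the RCT, yet Statistical methods chooses a model for its ability to use incomplete participants. Explaining withdrawal as closed course access does not help here, because waitlist members have no course access until the waiting period ends.

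Neither rule says what happens to data already collected.

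**The case against.** A reader might infer that all three rules delete data, so that the mixed model has no incomplete participants left to handle. The documents do not support that. Omission of data is stated only for outside therapy. Withdrawal by the team is explained as usually meaning closed course access, and Participants and recruitment separates leaving the program from having data excluded. The drop-out regression and the additional six-lesson completer analysis make sense only if non-completers stay in the main analysis. The other withdrawal reasons, such as a medication change, are discretionary and not tied to one arm, and nothing says that those records are removed. This objection stands, and it confines the definite error to the outside-therapy rule.

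A reader might also infer a material loss of power. Step 4 shows that the documented rule costs little against the planned 0.80, so no power claim is made.

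The sponsor could say that the aim is a comparison with people who receive no trauma therapy, which outside treatment would blur. That is a legitimate question, but it is not an intent-to-treat one. Deleting the whole record does not answer it either, because the remaining waitlist members are self-selected and the deletion discards scores collected before the outside therapy began.

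Finally, the share affected and its difference in outcome are assumed. At 5% omitted the distortion is small.

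**Conclusion.** The point holds in limited form. The outside-therapy rule is an explicit, one-arm exclusion after randomisation. It contradicts the intent-to-treat label and can bias the primary PCL-C contrast in a way that the mixed model cannot undo. On assumed shares of 5% to 20% and an assumed difference of 0.5 SD, the bias is 0.025 to 0.10 SD. Its direction cannot be determined from the documents. The contradiction itself needs no assumption; only its size does.

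The ten-week and questionnaire rules are ambiguous and conflict with neighbouring text. They should be reconciled, but they should not be read as stated deletions.

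**What to change.** Replace the outside-therapy omission rule with wording such as: *All randomised participants are analysed in their allocated arm using all outcome data collected, regardless of outside treatment, except where a participant asks for their data to be excluded.* The exception preserves the choice already given under Participants and recruitment.

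Alongside it:

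- Keep requesting the week-5 and week-11 questionnaires from waitlist members who start outside therapy.
- Record outside therapy from the SUDOR, which already has added items on other current treatment and is scheduled at mid- and post-treatment.
- Set aside data collected after outside therapy began only in a sensitivity analysis, with the same rule in both arms.
- Reconcile the two conditions for remaining in the trial with the adherence statement and with Statistical methods, and state that they do not govern which data are analysed. What they mean for course access is for the sponsor to settle and is outside this point.

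The planned sample size does not change and no visits are added. The cost is a wording amendment and updated participant information. Enrolment began in September 2014 and 26 people had met eligibility requirements when the article was submitted, so the change may need ethics approval and notice to waitlist participants who were told that their data would be omitted.
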